### Sample size

Sample size was calculated with regard to the two primary outcomes diet and PA. Based on a prevalence of fruit consumption reported in a previous study conducted at 64 German DFs including 2.658 preschoolers which reported rates of fruit consumption of 66.7% in the intervention group and 56% in the control group [23], we assumed a difference in the change in diet from baseline to 12-months follow-up of 8% between intervention and control group considering an estimated intracluster correlation coefficient (ICC) of 0.02, 90% power, and α = 0.05 (two-sided). Based on this, we estimated that a total of 1.020 children at 68 DFs would be required for our study. With regard to more conservative estimates for the ICC, this sample size will provide more than 80% power to detect changes of 8% in fruit consumption. We assumed a 25% loss to follow-up twelve months post-baseline. Therefore, we aim to reach 1360 children, in total, at baseline, twenty children at each of the 68 participating DFs. According to De Bock et al. [24], little is known about the extent to which PA-related outcomes in preschool children are inter-correlated. Therefore, our sample size calculation for detecting changes in objectively measured PA is based on the conservative assumption of an ICC of 0.1. To detect a difference of 0.5 standard deviations between intervention and control groups, we assumed a standard deviation of 38 counts per 15 s [24], a power of 90%, and α = 0.05 (two-sided), and estimated that a total of 360 children at 24 DFs will be necessary for our study. We increased our recruitment goal to 20 children per DF (240 per arm) to account for a 25% loss to follow-up. All power calculations were carried out in PASS [25], using tests for two proportions in a cluster-randomized design function.

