### Assessments

Children in each DF will be examined and tested during the same day. Anthropometric measures and motor tests will be performed in the gyms of the DFs between 8 a.m. and 4 p.m. during the day of the assessment. Children will not wear shoes during the weight and height measurements. To accomplish assessments, two study nurses will travel separately from DF to DF throughout Germany.

A portable stadiometer (Seca®, type 213) will be used to measure height and a body composition analyzer (TANITA®, BC 420 SMA) to measure weight and body composition (i.e., body-mass index, percent body fat). After the anthropometric measurements, children will participate in the whole battery of the KiMo test, a motor screening for preschool children aged three to six years consisting of five test items, each of them covering one motor ability relevant at the preschool age. A detailed description of the testing procedure is given by Klein and colleagues [26]. In summary, the tasks of this test (and the corresponding motor abilities in parentheses) are the following: 1) shuttle run (speed), 2) standing long jump (speed strength), 3) one leg stand (coordination, static balance), 4) sit and reach (flexibility), and 5) lateral jumping (coordination, strength endurance). Age- and gender-specific reference values are available for 3- to 6-year-old children. Test-retest values of the test demonstrated reliability and objectivity. Correlation coefficients amounted to *r* = .8 for the shuttle run, the standing long jump, lateral jumping, and the sit and reach; and a moderate correlation coefficient of *r* = 0.6 was found for the one leg stand [26]. Study nurses will be trained in administering this test prior to its use in the field.

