In a subsample of children at 24 DFs (12 intervention and 12 delayed intervention control DFs, ca. *n* = 360), PA will be assessed objectively using wrist-worn triaxial accelerometer watches (GENEActives, produced by ActivInsights Ltd.) for seven consecutive days at baseline and follow-up. The GENEActives provide raw accelerometry data in three axes (activity counts measured at 100 Hz) and measure surface skin temperature. They were chosen for the study because they are light-weight and waterproof and can be worn at the wrists meaning that they are more comfortable for continuous 24 h use among small children compared to the hip-worn version of the activity monitor. Compliance among small children has been shown to be greater when using wrist-worn accelerometers compared to hip-worn devices [27]. Reliability and validity of GENEActive measurements in children have been widely demonstrated for children above the age of eight years [28, 29]. The validity of this activity monitor for preschool-aged children is currently examined in another study [30]. Study nurses will mount the device on the left wrist because the majority of children is expected to be right-handed and it is recommended to use the non-dominant hand for measurement because energy prediction is more precise this way [29]. Handedness will also be assessed via parental questionnaire and controlled for in later statistical analysis. Parents of children of this subsample receive instructions regarding the recommended wear time and properties of the device, and a paper-and-pencil diary to report wear and non-wear times and to document reasons for not wearing the device.

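### Objective physical activity: the same number of accelerometer wearings spread over more of the 68 daycare facilities would be clearly more precise, if device recovery allows

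*Protocol article*

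**What the plan says.** The Sample size section sizes the trial on diet and PA, which it calls the two primary outcomes. For PA it states that "our sample size calculation for detecting changes in objectively measured PA is based on the conservative assumption of an ICC of 0.1". The target is half a standard deviation ("To detect a difference of 0.5 standard deviations between intervention and control groups"), with an SD of 38 counts per 15 s, 90% power and two-sided α of 0.05. The authors "estimated that a total of 360 children at 24 DFs will be necessary for our study", and then allow for dropout: "We increased our recruitment goal to 20 children per DF (240 per arm) to account for a 25% loss to follow-up".

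The Assessments section repeats the layout: "In a subsample of children at 24 DFs (12 intervention and 12 delayed intervention control DFs", with roughly 360 children, each wearing the device for seven consecutive days at baseline and at follow-up. The Abstract adds that these DFs are drawn at random within a geographic region.

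All 68 DFs have a target of twenty children and are measured at baseline and at twelve months. For this, "two study nurses will travel separately from DF to DF throughout Germany", and these nurses also put the device on the child's wrist. The article gives no reason for limiting the devices to 24 DFs. It states neither the number of physical devices nor how they are returned.

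**The concern.** The recruitment goal of 20 children per accelerometer DF equals the target for every DF. The subsample therefore takes essentially all participating children in 24 DFs and none in the other 44. With an assumed ICC of 0.1, later children in the same DF add progressively less information. With 12 DFs per arm, the effective sample size cannot exceed 12 / 0.1 = 120 per arm, however many children wear a device.

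At stake is the precision of the accelerometer comparison, which is one of the two outcomes that determine the trial's size. A nurse is already at each of the other 44 DFs on the assessment day, so fitting a few devices there needs no further measurement visit. A wider layout would also bring the objective PA comparison closer to the 34 versus 34 DFs that supply the other outcomes.

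**Working it through.** **Inputs (Sample size and Assessments sections).** ICC 0.1; SD 38 counts per 15 s; difference 0.5 SD = 19 counts; two-sided α 0.05; 24 DFs, 12 per arm; 20 children fitted per DF, 25% loss, so 15 analysed. Totals: 24 × 20 = 480 fitted and 480 × 0.75 = 360 analysed.

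**Formulas.** With k DFs per arm and m analysed children per DF:
- design effect DE = 1 + (m − 1) × ICC
- effective n per arm = k × m / DE
- SE in SD units = √(2 / effective n)
- power = Φ(0.5 / SE − 1.96), or from a noncentral t distribution on 2k − 2 degrees of freedom. Results are shown as normal / t.

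**The plan's own figure.** DE = 1 + 14 × 0.1 = 2.40. Effective n = 180 / 2.40 = 75 per arm. SE = √(2/75) = 0.163 SD, or 6.21 counts. Power is 86.5% / 83.3%, so the stated 90% is not reproduced. Without clustering, 90% power needs 85 children per arm. Multiplied by 2.40 this is 204 per arm, or 408 in total, against the 360 stated.

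**Alternative layouts**, with about the same number of wearings, ICC 0.1 and 25% loss:

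| Layout (DFs × fitted) | Fitted | Analysed per DF | DE | Effective n per arm | Power (normal / t) | Variance cut |
|---|---|---|---|---|---|---|
| 24 × 20 (plan) | 480 | 15 | 2.40 | 75 | 86.5% / 83.3% | – |
| 34 × 14 | 476 | 10.5 | 1.95 | 92 | 92.3% / 90.7% | 18% |
| 48 × 10 | 480 | 7.5 | 1.65 | 109 | 95.8% / 95.1% | 31% |
| 68 × 7 | 476 | 5.25 | 1.425 | 125 | 97.7% / 97.4% | 40% |

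The variance cut is 1 minus the ratio of effective sample sizes. For 68 × 7 it is 1 − 75.0/125.3 = 0.40.

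**Sensitivity to the ICC**, 68 × 7 against 24 × 20:

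| ICC | Effective n per arm, plan | Effective n per arm, 68 × 7 | Variance cut | Power, plan (normal / t) |
|---|---|---|---|---|
| 0.02 | 140.6 | 164.5 | 15% | 98.7% / 98.0% |
| 0.05 | 105.9 | 147.2 | 28% | 95.3% / 93.5% |
| 0.10 | 75.0 | 125.3 | 40% | 86.5% / 83.3% |
| 0.15 | 58.1 | 109.0 | 47% | 76.9% / 73.1% |

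The value 0.02 is the one the plan uses for diet. The values 0.05 and 0.15 are assumptions made here to show the range.

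**The case against.** **This is an efficiency preference.** More clusters with fewer children in each wins at any positive ICC, so the same remark fits most cluster subsamples. The three places that describe the 24-DF layout agree with one another, and keeping it causes no bias and no invalid inference. This stands, and it limits the point to an improvement.

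**There may be a logistic reason.** Drawing the DFs within a geographic region suggests deliberate containment of the device work, and a journal article may leave field logistics to the full protocol. This also stands.

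**The change may not be free.** A reader might infer that it costs nothing because nurses visit every DF anyway. The documents support that only for fitting. The device comes off about a week after the assessment day, and its recovery is not described. If staff collect devices, 68 DFs would mean collection at 44 more sites at each of two time points. Likewise, 480 counts children to be fitted, not physical devices.

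**Children still matter.** It is tempting to say that precision depends on the number of DFs and not of children, or that this is the least efficient layout possible. Neither holds. In the plan's layout the variance is proportional to 0.1 + 0.9/15 = 0.16, of which 0.06, or 37.5%, is the child-level part. Fewer than 24 DFs would be worse.

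**The ICC may be lower.** The plan itself speaks of a "conservative assumption of an ICC of 0.1", and adjusting for baseline and confounders may reduce the residual ICC. The gain then shrinks, and at 0.05 or below the plan's layout already exceeds 90% power. The plan chose 0.1 because little is known about clustering of PA at this age, and a wider layout gives protection if the true value is higher.

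**Conclusion.** The point holds as a worthwhile improvement with a named logistic cost. On the plan's own inputs, 24 DFs with 15 analysed children each give 83–86% power for 0.5 SD. About the same number of wearings gives 91–92% over 34 DFs, 95–96% over 48 and 97–98% over 68. The variance reduction from using all 68 DFs is about 40% at ICC 0.1, falling to about 28% at 0.05 and 15% at 0.02.

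These figures assume 25% loss in every layout, equal cluster sizes and no gain from covariate adjustment.

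The gap between 83–86% and the stated 90% does not by itself call for a move to 68 DFs. By the normal approximation, 28 DFs with 15 analysed children each would also close it (effective n 210 / 2.40 = 87.5 per arm, power 91%), though with 420 analysed children instead of 360. The argument for spreading is that it gains precision without more wearings.

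**What to change.** In the Abstract (Methods/design), Sample size and Assessments sections, replace 24 DFs with 20 children each by the widest layout that device recovery allows: 68 DFs with 7 fitted children each, otherwise 48 with 10, otherwise 34 with 14, split equally between arms. State that the research institute draws these children at random from each DF's list of consented children. Restate the objective PA power for the chosen layout, and say how devices are returned.

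Cost: no extra child and about the same number of wearings (476 to 480). Devices, diaries and parent instructions must be handled at 10, 24 or 44 more DFs at both time points, a within-DF draw is needed, and the geographic restriction is relaxed. The size of the recovery cost is an assumption: small if devices are posted back, larger if staff must collect them.

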### Assessments

Children in each DF will be examined and tested during the same day. Anthropometric measures and motor tests will be performed in the gyms of the DFs between 8 a.m. and 4 p.m. during the day of the assessment. Children will not wear shoes during the weight and height measurements. To accomplish assessments, two study nurses will travel separately from DF to DF throughout Germany.

A portable stadiometer (Seca®, type 213) will be used to measure height and a body composition analyzer (TANITA®, BC 420 SMA) to measure weight and body composition (i.e., body-mass index, percent body fat). After the anthropometric measurements, children will participate in the whole battery of the KiMo test, a motor screening for preschool children aged three to six years consisting of five test items, each of them covering one motor ability relevant at the preschool age. A detailed description of the testing procedure is given by Klein and colleagues [26]. In summary, the tasks of this test (and the corresponding motor abilities in parentheses) are the following: 1) shuttle run (speed), 2) standing long jump (speed strength), 3) one leg stand (coordination, static balance), 4) sit and reach (flexibility), and 5) lateral jumping (coordination, strength endurance). Age- and gender-specific reference values are available for 3- to 6-year-old children. Test-retest values of the test demonstrated reliability and objectivity. Correlation coefficients amounted to *r* = .8 for the shuttle run, the standing long jump, lateral jumping, and the sit and reach; and a moderate correlation coefficient of *r* = 0.6 was found for the one leg stand [26]. Study nurses will be trained in administering this test prior to its use in the field.

In a subsample of children at 24 DFs (12 intervention and 12 delayed intervention control DFs, ca. *n* = 360), PA will be assessed objectively using wrist-worn triaxial accelerometer watches (GENEActives, produced by ActivInsights Ltd.) for seven consecutive days at baseline and follow-up. The GENEActives provide raw accelerometry data in three axes (activity counts measured at 100 Hz) and measure surface skin temperature. They were chosen for the study because they are light-weight and waterproof and can be worn at the wrists meaning that they are more comfortable for continuous 24 h use among small children compared to the hip-worn version of the activity monitor. Compliance among small children has been shown to be greater when using wrist-worn accelerometers compared to hip-worn devices [27]. Reliability and validity of GENEActive measurements in children have been widely demonstrated for children above the age of eight years [28, 29]. The validity of this activity monitor for preschool-aged children is currently examined in another study [30]. Study nurses will mount the device on the left wrist because the majority of children is expected to be right-handed and it is recommended to use the non-dominant hand for measurement because energy prediction is more precise this way [29]. Handedness will also be assessed via parental questionnaire and controlled for in later statistical analysis. Parents of children of this subsample receive instructions regarding the recommended wear time and properties of the device, and a paper-and-pencil diary to report wear and non-wear times and to document reasons for not wearing the device.

The parental questionnaire will include parent-reported height and weight of the children, as well as self-reported height and weight of the parents, and items assessing behavioral and socio-demographic characteristics of both, children and parents. To assess the socioeconomic status of families included in the study, information on education and professional status of parents, as well as total income available to the family household, will be collected. Questions regarding migration background will include nationality, country of birth, year of immigration of both parents, and languages spoken at home. For information about the medical history of children, a selected number of physician-diagnosed chronic conditions (e.g., hayfever, atopic dermatitis, and asthma) will be included in the questionnaire, as well as items for assessing days of sickness and doctor’s visits during the past 12 months. Selected socio-demographic characteristics and health behaviors are also assessed in DF staff. Baseline and follow-up questionnaires employed at intervention and delayed intervention control DFs will be identical (for further detail, see Table 1).

**Table 1 Tab1:** Overview of the content of the questionnaires employed in the study

Assessment method	Measure of interest	Variables	Instrument/Scale
PARENTAL QUESTIONNAIRE			
Characteristics of parents	Socio-demographic characteristics	Age, education, employment, net household income, migration background	KiGGS [34]^a^
	Health	Height, weight, self-rated health status	SF-12, only one item [35]
	Smoking	Current smoking, intention to quit	HAPA, intention [36]
	PA	PA and sports activities during past three months, intention to engage in PA	DEGS [37]^b^, HAPA, intention [36]
	Diet	Intention to consume fruits and vegetables	HAPA, intention [36]
	Family climate	Health behaviors performed and health information available in the family context	FHC-scale [38]
Characteristics of children	Socio-demographic characteristics	Age, sex	
	Health	Height, weight, days of sickness, parent-rated health status, physician-diagnosed chronic conditions, doctor’s visits	SF-12 [35], KiGGS [34]^a^
	Diet	Consumption of un-sweetened beverages, fruits and vegetables, milk products, snacks, number of meals per day	Self-developed quantitative FFQ
	PA	Hours per week of moderate to intense PA and sports club membership	IDEFICS [39]^c^
	Media consumption	Time spent watching TV, video, DVD or using the computer, tablet, smartphone or game console	IDEFICS [39]^c^
	Mental well-being	Health-related quality of life, psychological attributes	Kiddy-KINDL^R^ [40], SDQ [41]
DF STAFF QUESTIONNAIRE			
Characteristics of DF staff	Socio-demographic characteristics	Age, sex, employment, migration background	DEGS [37]^b^
	PA	Work activity, sports activity, leisure-time activity; intention to engage in PA	Baecke questionnaire [42], HAPA, intention [36]
	Diet	Consumption of un-sweetened beverages, fruits and vegetables, milk products, snacks, number of meals per day; intention to consume fruits and vegetables	Self-developed quantitative FFQ, HAPA, intention [36]
	Smoking	Current smoking, intention to quit	HAPA, intention [36]
	Health	Self-rated health status, health-related quality of life, use of healthcare services, preventive health check-up program, preventive services (past 12 months)	SF-12 [35], DEGS [37]^b^
	Self-efficacy	General self-efficacy	GSE [43]
	Mental well-being	Stress	PSS4 [44]
	Health literacy	Knowledge, motivation and competences to access, understand, appraise, and apply health information	HLS-EU-Q47 [45]

Abbreviations: *DEGS* German Health Interview and Examination Survey for Adults, *FFQ* Food Frequency Questionnaire, *FHC* Family Health Climate, *GSE* General Self-Efficacy, *HAPA* Health Action Process Approach, *HLS-EU* European Health Literacy, *KiGGS* German Health Interview and Examination Survey for Children and Adolescents, *IDEFICS* Identification and Prevention of Dietary and Lifestyle induced Health Effects in Children and Infants, *KINDL*
^R^ revised questionnaire to assess Health-Related Quality of Life in children and adolescents, *PA* Physical activity, *PSS4* Perceived Stress Scale, *SF-12* Short Form-12, *SDQ* Strengths and Difficulties Questionnaire

^a^Items regarding socio-demographic characteristics of parents will be taken from the parental questionnaire for 3–6 year-olds from the KiGGS

^b^Items regarding parental PA and DF staff’s health and socio-demographic characteristics will be taken from the health questionnaire for 18–64 year-olds of the DEGS

^c^Items regarding children’s PA and media consumption will be taken from the parental questionnaire of the IDEFICS study

Six months after the launch of the program, computer-assisted telephone interviews (duration: ca. 20 min) will be conducted with DF staff in charge of implementation at all intervention DFs. Changes in institutional structures and processes that may facilitate the implementation of the program (e.g., provision of un-sweetened beverages at a regular basis, creation of space in the DFs enabling children to engage in active play [outside areas, gyms]) will be assessed.

### Follow-up assessment and delayed intervention

The follow-up assessment will take place approximately twelve months post-baseline and the same tests and questionnaires will be employed as those employed during baseline assessment. After completion of the follow-up assessment, the program will be made available to the delayed intervention control DFs. However, program implementation and changes in the outcomes which were assessed at the intervention DFs will not be further tracked at delayed intervention control DFs.

### Intervention

The three-year program ‘JolinchenKids - Fit and Healthy in Daycare’ was originally designed by the German health insurance AOK (see https://bremen.aok.de/inhalt/jolinchenkids-2/ for further detail). It is comprised of five modules, three focusing on children, one on parental participation in the program, and one on promoting health among DF staff. DFs are free to choose which modules they would like to implement and in which order meaning that there is no fixed time schedule to follow in regard to the implementation of these modules. The three modules focusing on children’s health are designed to affect dietary and PA habits among 3- to 6-year-olds and to improve their mental well-being. Instructions for intervention implementation are outlined in a detailed manual and DF staff receives training in one two-day workshop before the start of the program.

Activities of the *diet module* include small changes in the DF environment. For example, un-sweetened beverages, such as tea and water, are made available throughout the day in the groups (“drinking oasis”) and a healthy breakfast buffet is offered once every week (in existing or newly created areas in those DFs that did not have eating areas before). Furthermore, children are offered raw foods (e.g., fruits) twice every day. Examples for program activities in the *PA module* include the provision of a box with cards for kindergarten teachers with instructions for PA games with children. Also, intervention efforts are put into providing or creating areas with sufficient space at DFs so that children can involve in active play. The program recommendation for PA is at least one hour per week of engagement in PA games. The module focusing on *mental well-being* includes, among other materials, the provision of a card box with techniques for stress management to be implemented by DF staff during the day (program recommendation: one hour per week). Further, a space in the group room is created that children can take breaks in when they need them. The module focusing on *parental participation* in program activities includes several actions to encourage parents to support program implementation, such as parental participation in small implementation teams at DFs that plan implementation at the individual facility. DF staff is trained in how to involve parents in the program during a one-day workshop. In addition, materials for health education are distributed to parents in the form of newsletters (once per year per intervention module) or so called “messages in a bottle” (i.e., take home instructions for PA games or recipes for healthy meals). The fifth module is focused on *health promotion among DF staff*. DF staff is provided with a brochure containing information regarding health behavior change and the incorporation of health behavior in day-to-day activities at the DF. Furthermore, staff at the DFs is offered one educational workshop entitled “Fit at the job” lead by employees of the health insurance during which information on how to live a healthier lifestyle is provided to staff. Furthermore, counseling and classes (e.g., progressive muscle relaxation, pilates, nordic walking) are offered to DF staff by the health insurance at a regular basis. Table 2 provides further detail on the intervention components.

**Table 2 Tab2:** Overview of the intervention components of ‘JolinchenKids - Fit and Healthy in Daycare’

Module “Diet”	
(1) DF environment	• “drinking oasis” and “colorful garden” (un-sweetened beverages throughout the day, raw foods twice per day)
(2) Wooden train	• consisting of six wagons, each of them representing a food group; to be used by DF staff to teach children about food groups
(3) Card box “Healthy-and-tasty-land”	• one activity/ game per week (e.g., excursion, recipe, quiz)
(4) Healthy breakfast buffet	• once per week
(5) Joint activities with parents	• twice per year (e.g., sugar quiz)
(6) Newsletters	• e.g., instructions for healthy recipes distributed to parents once per year
Module “Physical Activity”	
(1) DF environment	• creating areas with sufficient space for active play
(2) Card box “Get-fit-in-the-jungle”	• at least one hour per week of engagement in PA games to enhance static balance, flexibility, strength, endurance, and speed
(3) Joint activities with parents	• twice per year (e.g., “family olympics”)
(4) Newsletters	• e.g., general information about PA, ideas for PA games to be included in everyday family life distributed to parents once per year
Module “Mental Well-being”	
(1) DF environment	• creation of a space where children can take breaks
(2) Card box “Feel-good-island”	• use of the hand puppet named “Jolinchen”
	• one hour per week (e.g., handling of conflicts, identifying and describing emotions)
	• short timeouts when needed (e.g., employment of techniques for stress management)
(3) Workshop for parents entitled “How to nurture children’s wellbeing”	• once per year executed by DF staff
(4) Joint activities with parents	• twice per year
(5) Newsletters	• information about card box topics distributed to parents once per year (e.g., identifying and describing emotions, handling of conflicts, stress management, strengthening of self-image of children)
Module “Parental Participation”	
(1) “JolinchenKids” team	• establishment of a team to organize implementation (DF administrator, DF staff, parents)
(2) Workshop “How to engage parents” for DF staff	• executed once during the 3-year implementation period by employees of the health insurance
(3) Manual “Parents are joining”	• practical information for DF staff about how to engage parents in program activities
(4) Card box “Joint activities with parents”	• general information about joint activities with parents
(5) Newsletters	• module-specific information and suggestions regarding games to be integrated into day-to-day family life distributed to parents once per year per module
(6) “Message in a bottle”	• take home instructions for PA games or recipes for healthy meals to be distributed to each child for a time period of two weeks
Module “Health Promotion among DF staff”	
(1) Workshop “Fit at the job”	• once in three years executed by employees of the health insurance
(2) Manual “How to live healthier”	• information regarding health behavior change and the incorporation of health behavior in day-to-day DF activities
(3) Further counseling and classes	• preventive healthcare services provided by the health insurance (e.g., classes in progressive muscle relaxation, pilates, nordic walking)

